## Abstract

**Background:**

Unexpected obstetric emergencies threaten the safety of pregnant women. As emergencies are rare, they are difficult to learn. Therefore, simulation-based medical education (SBME) seems relevant. In non-systematic reviews on SBME, medical simulation has been suggested to be associated with improved learner outcomes. However, many questions on how SBME can be optimized remain unanswered. One unresolved issue is how '*in situ* simulation' (ISS) versus 'off site simulation' (OSS) impact learning. ISS means simulation-based training in the actual patient care unit (in other words, the labor room and operating room). OSS means training in facilities away from the actual patient care unit, either at a simulation centre or in hospital rooms that have been set up for this purpose.

**Methods and design:**

The objective of this randomized trial is to study the effect of ISS versus OSS on individual learning outcome, safety attitude, motivation, stress, and team performance amongst multi-professional obstetric-anesthesia teams.

The trial is a single-centre randomized superiority trial including 100 participants. The inclusion criteria were health-care professionals employed at the department of obstetrics or anesthesia at Rigshospitalet, Copenhagen, who were working on shifts and gave written informed consent. Exclusion criteria were managers with staff responsibilities, and staff who were actively taking part in preparation of the trial. The same obstetric multi-professional training was conducted in the two simulation settings. The experimental group was exposed to training in the ISS setting, and the control group in the OSS setting. The primary outcome is the individual score on a knowledge test. Exploratory outcomes are individual scores on a safety attitudes questionnaire, a stress inventory, salivary cortisol levels, an intrinsic motivation inventory, results from a questionnaire evaluating perceptions of the simulation and suggested changes needed in the organization, a team-based score on video-assessed team performance and on selected clinical performance.

**Discussion:**

The perspective is to provide new knowledge on contextual effects of different simulation settings.

**Trial registration:**

ClincialTrials.gov NCT01792674.

## Background

Care for pregnant and parturient women is a field where unexpected emergencies occur; for example, emergency Caesarean section, postpartum bleeding or severe pre-eclampsia, that may potentially harm both mother and baby [1-4]. Since obstetric emergencies are rare and hence by nature difficult to learn in real life, simulation-based medical education (SBME) is argued to be an essential remedy [5]. SBME is defined as “a person, device, or set of conditions which attempts to present education and evaluation problems authentically. The student or trainee is required to respond to the problems as he or she would under natural circumstances” [6].

Labor wards have a dual function in creating a relaxed atmosphere for normal childbirth and at the same time showing readiness to deal with life-threatening emergencies [7]. Labor wards are challenging work places and patient safety and medical litigation are high on the agenda [8-11]. In certain situations, clinical management of pregnant and parturient women may require the involvement of a variety of health-care professionals and medical specialties. The primary care team in a delivery room consists of a midwife assisted by an auxiliary nurse. In cases of emergencies, more experienced midwives and obstetricians will be called for assistance. If the clinical situation progresses further to an emergency, an anesthesiologist, a nurse anesthetist and the operating room personnel may become involved. Occasionally, involvement of other specialties may also be required, when a rather common clinical event has evolved into a potentially life-threatening situation calling for multi-professional and multi-disciplinary clinical management.

Such rare and complex clinical situations require complex skills, which cannot be trained and learned in clinical practice. Thus, there is a need for SBME in obstetric emergencies. In a systematic review of training in acute obstetric emergencies [12] the authors applied the quality assessment of diagnostic accuracy studies criteria. Out of 97 articles, only eight articles - four randomized trials and four cohort studies - assessing the effect of teamwork training in a simulation setting were identified. Based on these trials, it was concluded that teamwork training in a simulation-based setting resulted in improvements in knowledge, practical skills, communication, and team performance in acute obstetric situations. No difference in outcomes was found when comparing SBME in a dedicated simulation centre with SBME in a local hospital setting [13,14].

From the non-systematic reviews on SBME [6,15] and the obstetric systematic review [12] we can conclude that SBME in labor wards is worthwhile, and that multi-professional and multi-disciplinary team training are important approaches due to the complexities of the trained skills and the rarity of the high-risk obstetric emergencies. However, we need to further study key elements of SBME in order to fully understand how we can best improve SBME in obstetric emergencies. One potential element influencing the effect of simulation might be the level of authenticity of the simulation or, in other words, the fidelity of the simulation. Fidelity is described as a multi-dimensional concept consisting of different parts: 1) physical/functional or engineering fidelity, which mean the degree to which the simulator duplicates the appearance and perception of the real system; 2) psychological fidelity is the degree to which the trainee perceives the simulation to be an authentic surrogate for the trained task. The literature states that psychological fidelity is considered to be the most essential requirement when conducting team training [16,17]. The simulation setting has traditionally been 'off site simulation' (OSS), either at a simulation centre or in local facilities in the hospital set up for the single purpose of simulation training. However, more recently, a new simulation modality, the '*in situ* simulation' (ISS), has been introduced. ISS is described by Riley and colleagues [18] as “a team-based simulation strategy that occurs on the actual patient care units involving actual healthcare team members within their own working environment”. An unanswered question is whether ISS is superior compared with OSS with regards to simulation-based learning in obstetric emergencies? We hypothesized that the psychological fidelity is influenced by the setting in which the simulation training is conducted, and that ISS can add to the level of fidelity and therefore be more effective.

Apart from a few larger observational studies within different medical specialties [18-20], most of the studies conducted on ISS describe a local educational intervention with a local ISS program. Methodologically, the studies are descriptive and few include a control group or pre- and post-tests, and we have not been able to identify any randomized trials [21]. It is argued that ISS can identify system weaknesses because ISS takes place in the real working environment and, therefore, potentially has more psychological fidelity as opposed to OSS [18-22], and ISS can be used to test how new processes are functioning in clinical facilities [23]. Some argue that ISS overcomes feasibility issues and is cost saving compared to OSS in simulation centers [24,25]. ISS can consist of either an announced training event or an unannounced event. Anderson and colleagues [26] focused on unannounced ISS and its potential disadvantages, and argued how unannounced ISS is time consuming and may intimidate participants.

Human factors such as stress and motivation impact learning [27-31]. Studies show that simulation can be a stressor. High stress responsiveness has been associated with both enhanced and impaired performance, but with enhanced learning [29]. As such, further exploration of these issues is needed. Experimental studies have used unspecific measurements of stress level [32], and different stress inventories as well as measurements of salivary cortisol levels [28,33-36]. Motivational processes are central to learning [27,30,37], and as part of this trial we will investigate phenomena such as intrinsic motivation, and how this is moderated by the two different training settings (ISS versus OSS). We hypothesize that, in simulation-based training in obstetric emergencies, ISS is more effective than OSS regarding learning. We anticipate that the participants will experience ISS as more demanding, and that ISS will create higher levels of stress and motivation, which may yet again enhance learning. Further, we hypothesize that ISS training may provide the investigators with more information on changes needed in the organization than OSS training will. Randomized trials are needed to obtain knowledge on the effect of ISS versus OSS on participants and its advantages and disadvantages.

## Methods and design

The design is a single-center, investigator-initiated randomized superiority trial.

### The setting

The trial was undertaken at Rigshospitalet, Copenhagen University Hospital, in an obstetric and anesthesia high-risk department with approximately 6,600 deliveries per year. The intervention period was scheduled to run through April to June 2013, and follow-up by questionnaires until August 2013.

### Participants

All health-care professionals from the department of obstetrics and anesthesia, Juliane Marie Centre for Children, Women and Reproduction, Rigshospitalet, working on or in relation to the labor ward, were eligible for inclusion in the trial. These health-care professional groups, who were working on shift, encompassed: specialized obstetricians; trainee obstetricians; midwives; specialized midwives; auxiliary nurses; specialized anesthesiologists; trainee anesthesiologists; nurse anesthetists; and surgical nurses. Participants gave informed consent. Exclusion criteria were lack of informed consent, employees with managerial and staff responsibilities, staff members involved in the design or conduction of the trial, and finally employees who did not work in shifts.

### Randomization

Randomization was done by the Copenhagen Trial Unit, using a computer-generated allocation sequence concealed to the investigators. The randomization was conducted in two steps. The participants were individually randomized into the experimental group (ISS) or the control group (OSS). The allocation sequence was stratified according to health-care professional groups in order to resemble authentic teams and according to the days they were available for training. After individual randomization, the participants in either group (ISS and OSS) were randomized into five teams each.

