### Trial interventions

This trial included an experimental educational intervention ISS [18,21], which means training in the actual patient care unit (in other words, the labor room and operating theatre). The experimental intervention in the present trial was pre-announced ISS. We planned to conduct announced ISS training, as the complexity of conducting unannounced ISS sessions with the involvement of health-care professionals on a larger scale is unrealistic taking into consideration work schedules and the daily clinical work activities. Training of the control group (OSS) took place in training rooms that were set up for the occasion in the hospital, but away from the actual patient care unit.

The simulated scenarios applied in the trial were contained in a full training day. The development of the curriculum for the training day was based on an instructional design approach [38,39] and was developed and pilot tested by a local multi-professional working committee. In January 2012 this working committee was appointed by the managerial groups of the departments of anesthesia and obstetrics and consisted of representatives from all the health-care professionals who will participate in the trial. This working committee developed aims and objectives based on the principles of Blooms taxonomy [40], and the aims and objectives were approved by the management groups. The simulated scenarios in ISS and OSS were designed in a way that involved both the labor room setting and the operating theatre, to specifically focus on the patient journey and the communication amongst health-care professionals during patient transfers, where many different health-care professionals and different medical disciplines are involved. This approach to training was chosen based upon previous experience with obstetric simulation-based training conducted in the obstetric department [32,41] and was designed in accordance with the overall plan of strategy of the obstetric department and the anesthesia department, Juliane Marie Centre for Children, Women and Reproduction, Rigshospitalet [42].

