### Sample size calculation

There are no data on training effectiveness of ISS upon which to base sample size calculations. We chose to calculate the required sample size based on experience with knowledge tests from data in previous studies [13,32]. We were planning a trial of a continuous response variable from independent control and experimental participants with one control per experimental participant. We assumed the response within the experimental and the control group to be normally distributed with a standard deviation of 24%. If the true difference in the experimental and control means was 17%, we needed to study 32 experimental participants and 32 control participants (a total of 64) to be able to reject the null hypothesis; that is, that there was no difference in population means of the experimental and control groups with a probability of (power) 80%. The two-sided type I error probability associated to test this null hypothesis was 5%.

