### Sample size estimation adjusted for clustering

As the intervention was delivered in teams (clusters), observations on participants in the same team were likely to be correlated. Hence the effective sample size was less than that suggested by the actual number of individual participants. The reduction in effective sample size depends on the intra-class or cluster correlation coefficient (ICC) [57,58]. In order to adjust the sample size for this, the crude sample size calculated above needed to be multiplied by the design effect. The cluster size was ten, as there were ten participants in each team, and we assumed the ICC to be 0.05 [58]. Design effect = 1 + (cluster size – 1) × ICC → design effect = 1.45. Accordingly, the sample size was then 64 × 1.45 = 92.8 participants. We therefore planned to include 100 participants in the experimental and control groups (50 in each group) each of which consists of five teams of 10 participants in each arm. Statistical methods for the primary and exploratory outcome of the hypotheses are laid out in Table 2, and also the statistical methods are described. The intervention was delivered in teams, which means that participants were clustered within teams. Since observations from individuals in the same team are potentially correlated we will use generalized estimating equations (GEE) [59] in the parametric analyses to take this cluster effect into account. The statistical analysis will be adjusted for health-care professional groups. The experimental group (participants or teams in ISS) will be compared against the control group (participants or teams in OSS) for all analyses. The results will be expressed by means with standard deviations and confidence intervals, as well as by medians with percentiles. Associated *P*-values and effect sizes will be reported.

For the interval scale data, linear regression will be used to analyze changes between the experimental and the control group from baseline to peak. GEE will be used to take the clustered nature of the data into account. Non-parametric statistical analyses will be used for the ordinal scale data. Medians and percentiles will be reported and the Mann–Whitney U test will be used. Individual responses to the evaluation questionnaire are measured on a Likert scale and will be treated as ordinal data and analyzed at the item level.

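### Availability for training is a stratification factor in the allocation but is absent from the stated adjustment: a minor, conditional loss of precision

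*Protocol article*

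**What the plan says.** Under Randomization, the protocol names two stratification factors. The first is profession: "The allocation sequence was stratified according to health-care professional groups in order to resemble authentic teams". The second follows in the same sentence: "according to the days they were available for training". Teams are then formed within each arm: "After individual randomization, the participants in either group (ISS and OSS) were randomized into five teams each".

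The adjustment is stated under Sample size estimation adjusted for clustering: "The statistical analysis will be adjusted for health-care professional groups". Clustering by team is covered in the same section: "we will use generalized estimating equations (GEE) [59] in the parametric analyses to take this cluster effect into account". Neither that section nor Table 2 mentions availability days, and no reason is given for leaving them out.

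Under Trial interventions, the training unit is a single day: "The simulated scenarios applied in the trial were contained in a full training day". The protocol does not give the number of availability strata. It also does not say whether they coincide with team training days, or whether in situ (ISS) and off site (OSS) teams are matched on date.

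**The concern.** When the arms are balanced on a factor that predicts the outcome, the treatment difference gains precision. If that factor is then left out of the model, its variance stays in the error term. The reported standard error misses the gain, so the interval is too wide and the test conservative.

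There are plausible routes by which date could matter. Training ran from April to June 2013 (The setting). The knowledge test was taken on the training day itself (Table 1). The Discussion accepts that staff in the two arms mix and may pass on information, so later teams could score differently from earlier ones. With ten teams, precision at team level is scarce. The protocol gives no figure for any date effect, so only a range that includes zero can be shown.

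**Working it through.** **Inputs.** From Sample size calculation: responses "normally distributed with a standard deviation of 24" points; "If the true difference in the experimental and control means was 17" points; 80% power; two-sided 5%. From the section on clustering: ICC 0.05, five teams of 10 per arm.

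**The plan's own figure.** n per arm = 2 × (1.96 + 0.842)² × 24² / 17² = 31.3, so 32 per arm and 64 in total. The design effect is 1 + 9 × 0.05 = 1.45, and 64 × 1.45 = 92.8. This reproduces the plan. Neither stratification factor enters the calculation.

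**Standard error without a day term.** The total variance is 24² = 576.
- Between-team part: 0.05 × 576 = 28.8.
- Within-team part of a team mean: 0.95 × 576 / 10 = 54.7.
- Variance of a team mean: 83.5.
- SE of the arm difference: √(2 × 83.5 / 5) = 5.78.
- 95% half-width on 8 df: 2.306 × 5.78 = 13.3 points.

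**Assumed layout.** There are five day blocks, each with one ISS and one OSS team. Day explains a share f of the 28.8. The error that remains after balancing on day is 28.8(1 − f) + 54.7:
- f = ½: 69.1, SE 5.26. The unadjusted SE is √(83.5/69.1) = 1.10 times as large.
- f = 1: 54.7, SE 4.68. The ratio is √(83.5/54.7) = 1.235.

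For a fixed linear trend over five equally spaced days, the sample variance of the day effects is 5/4 of the population value. The unadjusted half-width becomes 2.306 × √(2 × (14.4 × 1.25 + 69.1) / 5) = 13.6 at f = ½. At f = 1 it is 2.306 × √(2 × (28.8 × 1.25 + 54.7) / 5) = 13.9.

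**With a day term.** A 1-df term leaves 7 df (t = 2.365). If it captures the whole day effect, the half-width is 2.365 × 5.26 = 12.4 or 2.365 × 4.68 = 11.1. If day is irrelevant it is 2.365 × 5.78 = 13.7. Five separate blocks leave 4 df (t = 2.776). The remaining entries come from 200,000 simulated trials per setting; the two-level split is the first two blocks against the last three.

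| Share f | No day term | Linear date term, linear trend | Two-level term, linear trend | Either 1-df term, unordered day effects | One effect per block |
|---|---|---|---|---|---|
| 0 | 13.3 | 13.7 | 13.7 | 13.7 | 16.0 |
| ½ | 13.3 (trend: 13.6) | 12.4 | 12.9 | 13.5 | 14.6 |
| 1 | 13.3 (trend: 13.9) | 11.1 | 12.1 | 13.3 | 13.0 |

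**Type I error without a day term, t on 8 df.** At f = ½ it is about 3.5% with unordered day effects and 3.1% with a linear trend. At f = 1 it is about 2.3 to 2.4% and 1.6%.

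**Strata spread within teams.** With day shares from 0 to 10% of the total variance (8,000 runs each), the estimated SE is 5.7 to 5.8 against a true 5.6 to 5.9. Type I error runs from 5.3% down to 4.3%, so the effect is negligible.

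**The case against.** The strongest reply is that nothing in the protocol shows that day affects the test score. Both arms follow one curriculum with standardised scenarios and trained educators. Availability may be no more than a rostering constraint, and its strata may not match training days. Team is already the GEE cluster, so correlation among people trained together enters the standard error. A condensed article may also leave covariate detail to an analysis plan. All of this limits the size of the point. It does not remove the mismatch: the article itself states the adjustment, and it names one of two randomisation factors without explanation.

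A second reply concerns the remedy. If day effects do not follow calendar order, a 1-df term recovers nothing, and one effect per block costs too many degrees of freedom unless day explains nearly all the between-team variance. If each team trained on its own date, day is confounded with team and cannot be fitted as separate effects at all. This stands, and it is why a gain is claimed only for a trend over time.

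A reader might infer that the planned standard errors are too small, or that false positives increase. The protocol states no standard error for the treatment effect, and omitting a balanced factor can only leave the estimate right or too large. Nor does the sample size change.

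The word conservative does presuppose a small-sample reference, which the article does not name. In 8,000 simulated trials with no day effect, an uncorrected sandwich SE with a normal reference gave a type I error of about 12% with ten teams, and about 15% with day blocks added in the same uncorrected way. That is a separate matter, not caused by this omission. It means that a day term should not be added without the correction.

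**Conclusion.** The allocation uses two factors and the stated adjustment uses one. The consequence is conditional. It needs outcomes to vary with training date, availability strata that coincide with training days, and arms balanced over those days. Under those conditions, with the protocol's SD and ICC and a t reference on 8 df, the test runs at about 3.1 to 3.5% when day explains half of the between-team variance, and at about 1.6 to 2.4% when it explains all. A linear date term would then save up to about 1 to 3 points of half-width if the effect is a calendar trend (13.6 to 12.4, or 13.9 to 11.1). It would save nothing if the day effects are unordered. Outside those conditions the omission is negligible. The point is minor: it concerns precision, not bias or validity.

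**What to change.** In the section Sample size estimation adjusted for clustering, state that the analysis is adjusted for both stratification factors. Enter availability or training day as one pre-specified 1-df term, preferably linear calendar time, because a two-level split recovers less. Do not fit one effect per day. Name a small-sample reference suited to ten teams, say how the availability strata relate to training days, and report the profession-only model as a sensitivity analysis. Settle this before the allocation is unblinded.

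The cost is a few sentences and one team-level degree of freedom. If day turns out to be irrelevant, the half-width grows from 13.3 to 13.7 points.
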